**The effect of Baduanjin exercise on physical and psychological wellbeing of college students: study protocol for a randomized controlled trial**

1. Study object

The primary aim of this trial is to evaluate the effectiveness and safety of Baduanjin exercise on physical and mental health of college students through a rigorous randomization, parallel-controlled design.

2. Method/design

2.1 Sample size

We use the improvement of lumbar flexion muscle strength as the main effect indicators to estimate the sample size, and our preliminary test data from 20 eligible participants indicated the means with standard deviation of the lumbar flexion muscle strength was 258.25 newton (N) and 114.19 N respectively. To detect a 20% mean difference on the Baduanjin exercise at the end of intervention, 101 participants per group are calculated according to the formula with a type I error of 5% (α= 0.05) and 90% power (β= 0.10). Assuming a dropout rate of 10% for follow-up, the sample size is 111 for each group.

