2.8 Statistical analysis

Baseline characteristics and outcomes between groups will compare using the t-test or non-parametric test for continuous variables and Pearson chi-squared or Fisher’s exact test for categorical variables. Subgroup analysis stratified by participants’ sex will be used for the primary outcomes.

All data will be analyzed with SPSS 21.0 (IBM, Chicago, IL, USA) software packages. The statistical significance is defined as two-sided P value of <0.05.

Participants recruitment

Eligible participants n=222

Baseline assessment

Exclusion (reasons): n=

Not meeting inclusion criteria: n=

Declined to participate: n=

Other reasons: n=

Randomization allocation

Baduanjin training group

n=111

Control group

n=111

Drop out (reasons): n=

Intervention group: n=

Control group: n=

Outcomes assessment after intervention: lumbar muscle strength, lumbar proprioception function, self-reported symptom intensity, stress, self-efficacy, attention, cardiopulmonary function, flexibility, hand grip strength, self-esteem, mood and mindfulness, quality of life, quality of sleep and adverse events

Follow up for 12 weeks

Lost to follow up: n=

Intervention group: n=

Control group: n=

Above outcomes assessment after follow-up period

Included analysis: n=

Intervention group: n=

Control group: n=

Statistic analysis

Excluded from analysis: n=

Intervention group: n=

Control group: n=

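### Section 2.1 gives 101 per group where its inputs give 103, and 111 does not fully cover 10% dropout, so expected power is about 89%, not 90%

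*Protocol*

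**What the plan says.** Protocol Section 2.1 sizes the trial on one variable: "We use the improvement of lumbar flexion muscle strength as the main effect indicators". The variability comes from 20 pilot participants, in whom the mean and SD of "the lumbar flexion muscle strength was 258.25 newton (N) and 114.19 N respectively". The target is set as follows: "To detect a 20% mean difference on the Baduanjin exercise at the end of intervention". The error rates are "a type I error of 5% (α= 0.05) and 90% power (β= 0.10").

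From these inputs the section reports that "101 participants per group are calculated according to the formula with a type I error of 5" per cent. It does not name or print the formula. It then adds: "Assuming a dropout rate of 10% for follow-up, the sample size is 111 for each group". It does not say how 101 became 111. Section 2.2 carries the result forward as 222 participants in total.

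Section 2.1 does not say whether the test is one- or two-sided. Section 2.8 does: "The statistical significance is defined as two-sided P value of <0.05". Section 2.3 fixes equal allocation.

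**The concern.** A sample size paragraph should let a reader get from the inputs to the number randomised. Here two steps fall short, both in the same direction. The number before dropout is lower than the usual formula gives. The dropout allowance then leaves fewer expected completers than the section itself says are required. If both hold, the stated power is higher than the design delivers on its own assumptions. The accuracy of the published power statement is at stake, and the size of the gap decides whether anything more is.

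**Working it through.** **Inputs**

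- Difference: 0.20 × 258.25 = 51.65 N (Section 2.1).
- SD: 114.19 N (Section 2.1). Standardised difference: 51.65 / 114.19 = 0.4523.
- Two-sided α = 0.05 (level from Section 2.1, sidedness from Section 2.8), so z = 1.95996.
- Power 90% (Section 2.1), so z = 1.28155.
- Allocation 1:1 (Section 2.3). Dropout 10% (Section 2.1).

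**Step 1. Number per group before dropout**

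n = 2 × (z₁₋α/₂ + z₁₋β)² × (SD / difference)²

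= 2 × (1.95996 + 1.28155)² × (114.19 / 51.65)² = 102.7, so 103.

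The same calculation with the noncentral t distribution gives 104. The protocol states 101.

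**Step 2. Where 101 might come from**

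- One-sided 5%: 83.7, so 84. This does not fit.
- Coarser normal quantiles (1.96 and 1.28): 102.6. This does not fit.
- Difference rounded from 51.65 N to 52 N: 100.9 to 101.4, depending on whether the SD is also rounded to 114 N and on the quantiles used. This comes close, so early rounding is a plausible source, but the protocol does not confirm it.

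**Step 3. Dropout**

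- 101 × 1.10 = 111.1, which matches the stated 111. The multiplication is inferred from this match.
- Completers expected from 111: 111 × 0.90 = 99.9, below 101.
- To keep 101 completers: 101 / 0.90 = 112.2, so 113.
- To keep 103 completers: 103 / 0.90 = 114.4, so 115 per group, or 230 in total. Against 111 (222 in total) the gap is 4 per group, and 4 / 115 = 3.5%.

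**Step 4. Power at the relevant numbers**

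Normal approximation: Φ(0.4523 × √(n/2) − 1.95996). The t-test version uses the noncentral t with 2n − 2 degrees of freedom and noncentrality 0.4523 × √(n/2).

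| Analysed per group | Normal | t-test |
|---|---|---|
| 99.9 (111 less 10%) | 89.2% | 88.9% |
| 101 | 89.5% | 89.2% |
| 103 | 90.1% | 89.8% |
| 104 | 90.3% | 90.1% |
| 111 (no loss) | 92.1% | 91.8% |

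At the expected number of completers, power is about 89% by either method, roughly one point below the stated 90%.

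**The case against.** The strongest reply is that the discrepancy is trivial. The stated 101 is only 2 below the normal result and 3 below the t result, and rounding the difference to 52 N gives about 101. That would be a rounding slip and not a wrong method. The dropout operation is nowhere stated, so the multiplication is only a good fit. Taken alone, the dropout step costs 2 per group (111 against 113). Only the two corrections together reach 115, and power still moves by about one point. The 10% loss is also described as being for follow-up. If part of it falls after the 13-week assessment, more than 100 per group would be available for the comparison on which the trial was sized.

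Most of this stands, and it limits how serious the point is. It does not remove it. Whatever formula gave 101, a 10% loss from 111 leaves fewer than 101, so the paragraph misses its own target.

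Two stronger readings are tempting. A reader might infer from the word improvement that the trial is to be analysed on change from baseline, so that the SD is the wrong one and power could be far from 90%. The protocol does not support this. Section 2.1 sets its target as a mean difference at the end of the intervention, and Section 2.8 compares outcomes between groups without specifying change scores. The SD of the strength value is the right input for that comparison. Power for a change score would need a baseline-to-follow-up correlation that the protocol does not give. The word is loose, no more. A reader might also object that an SD from 20 people is imprecise. That is true of any pilot of that size, the protocol states the number openly, and it is not an error in the plan.

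**Conclusion.** The point holds as a minor error in the text. On the stated inputs the standard formula gives 103 per group (104 by t-test) where Section 2.1 states 101, and the 111 randomised leave about 100 after the assumed loss. Expected power is 88.9% by t-test or 89.2% by the normal approximation.

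It would be wrong to conclude that the trial is materially underpowered or that its sample size has no traceable basis. The shortfall is about one percentage point, and with no dropout the 111 per group would exceed 90%.

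The result assumes a two-sided 5% test as in Section 2.8, an unadjusted comparison of two means with a common SD of 114.19 N, a true difference of 51.65 N, and the full 10% lost before the 13-week assessment.

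**What to change.** Keep 222 participants and restate the calculation in Section 2.1, for example:

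> The two-sided two-means formula requires 103 participants per group. Randomising 111 per group leaves about 100 after 10% loss, giving about 89% power by an unadjusted two-sided t-test for a 51.65 N difference in 13-week lumbar flexion strength (SD 114.19 N).

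Print the formula. Where the section calls the sizing variable an improvement, name the end-of-intervention value instead, since that is what the SD describes. If the sponsor prefers to retain the 90% claim, including the dropout allowance, the calculation should divide by 0.90, which gives 115 per group (230 in total).

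The first option costs one corrected paragraph and about one point of stated power. It adds no participants and changes no procedure.

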2.2 Participant and recruitment

We will recruit 222 college students from Fujian University of Traditional Chinese Medicine (FJTCM).

2.2.1 Inclusion criteria

(1) be aged 18 to 25 years;

(2) be able to give the informed consent form;

(3) be a fulltime student at first or second grade.

2.2.2 Exclusion criteria

(1) being or having been engaged in a long-term regular practice of Baduanjin;

(2) being a member of the Martial Arts Association, Dance Association, Aerobics Association, Sanda Association, or Taekwondo Association;

(3) those who have suffered from severe cardiovascular diseases, musculoskeletal system diseases, or other sports contraindications.

2.3 Randomization, allocation concealment and blinding

The random allocation sequence will be produced by an independent statistician using the statistical software SAS9.1. The participants will be allocated to either Baduanjin exercise or usual exercise control group according to 1:1 equal proportion rule. The random allocation sequence will be managed by a specified project manager who is not involved in the recruitment program.

The random allocation sequence will be managed by the project manager. The project manager and exercise coaches will be not involved in the assessment of outcome; and the outcome assessors and the statistic analyzer will be not involved in the participants’ screening and allocating.

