2.6.1 Primary outcomes

• Lumbar muscle strength consists of flexion, extension, lateroflexion, and rotation myodynamia. It will be assessed with the *Tergumed Work Station* (produced by Proxomed GmbH, Germany; product type: Flexion Work Station:Tergumed Flexion; Lateral Flexion Work Station: Tergumed lateral Flexion; Extension Work Station: Tergumed Extension; Rotation Work Station: Tergumed Rotation) by experienced operators at the Evaluation Department of Rehabilitation Hospital Affiliated to FJTCM.

• Lumbar proprioception function will be measured by the *Prokin* proprioception evaluation and training system (produced by Tecnobody .S.r.l, Italy; product type: PK254P) by the Evaluation Department of Rehabilitation Hospital Affiliated to FJTCM.

• The Symptom Checklist-90 (SCL-90) will be used to measure self-reported symptom intensity.

• Stress will be measured with the Chinese Perceived Stress Scale (CPSS).

• Self-efficacy will be assessed with General Self-efficacy Scale (GSES).

• Attention will be assessed by Schulte Grid (8*8) test.

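### Sex is the only named subgroup factor for the primary outcomes, but the stated analysis does not adjust for it and no stratification by sex is described: an avoidable loss of precision, not a bias

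*Protocol*

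**What the plan says.** On allocation, protocol section 2.3 gives the source of the sequence, "The random allocation sequence will be produced by an independent statistician using the statistical software SAS9.1", and the ratio, "The participants will be allocated to either Baduanjin exercise or usual exercise control group according to 1:1 equal proportion rule". It mentions neither strata nor blocks.

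On analysis, section 2.8 states "Baseline characteristics and outcomes between groups will compare using the t-test or non-parametric test for continuous variables", and "The statistical significance is defined as two-sided P value of <0.05". No covariate is named. The same section adds: "Subgroup analysis stratified by participants’ sex will be used for the primary outcomes".

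The first primary outcome in section 2.6.1 is lumbar strength: "Lumbar muscle strength consists of flexion, extension, lateroflexion, and rotation myodynamia". Lumbar flexion strength also drives the sample size in section 2.1. Sections 2.2.1 and 2.2.2 do not restrict sex, so a mixed sample is to be expected. Section 2.6 has every primary outcome measured at baseline, week 13 and week 25.

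**The concern.** The protocol itself treats sex as the participant characteristic that matters for the primary outcomes, and it names no other. Yet the main between-group comparison makes no use of sex, and the allocation as described does not balance it. For an outcome measured in newtons, sex could plausibly account for a sizeable part of the spread. The stated coefficient of variation of 114.19 / 258.25 = 44% is compatible with that but does not show it.

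Two things are at stake. Any variance due to sex stays in the error term of the t-test and costs power. And if the arms happen to differ in their sex mix, the observed strength difference moves with that mix, and the stated test has no means of taking it out.

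**Working it through.** **Inputs from section 2.1.** Mean 258.25 N and SD 114.19 N from 20 preliminary participants; target difference 20%, i.e. 0.20 × 258.25 = 51.65 N; α = 0.05 (two-sided by section 2.8); power 90%; 101 per group, 111 after dropout.

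**Assumptions not in the documents.** Sex difference in strength D = 80 to 150 N; share of men p = 30 to 50%.

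**1. The plan's own figure.** n = 2 × (1.960 + 1.282)² × (114.19 / 51.65)² = 102.7, so 103 per group. The stated 101 is within two participants of this. For dropout, 101 × 1.1 = 111.1, so 111. No stated figure needs correction on this point.

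**2. Share of variance due to sex.** R² = p(1 − p)D² / SD², with SD² = 114.19² = 13,039.
- Low end: 0.3 × 0.7 × 80² / 13,039 = 1,344 / 13,039 = 0.10.
- High end: 0.5 × 0.5 × 150² / 13,039 = 5,625 / 13,039 = 0.43.

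**3. Power with and without adjustment.** Use 100 per arm (111 × 0.9 = 99.9), a two-sided t-test and residual SD = 114.19 × √(1 − R²).

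| | Residual SD (N) | Power |
|---|---|---|
| Unadjusted | 114.19 | 88.9% |
| p = 0.3, D = 80 (R² = 0.10) | 108.2 | 91.9% |
| p = 0.3, D = 150 (R² = 0.36) | 91.2 | 97.9% |
| p = 0.5, D = 80 (R² = 0.12) | 107.0 | 92.5% |
| p = 0.5, D = 150 (R² = 0.43) | 86.1 | 98.8% |

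**4. How large a chance imbalance can be.** With 111 per arm and no stratification, the SD of the between-arm difference in the share of men is √(2p(1 − p) / 111) = 0.0615 at p = 0.3 and 0.0671 at p = 0.5. The 95% limits are 1.96 times these, ±12.1 and ±13.2 percentage points. A gap above 10 points has probability 10 to 14% by the normal approximation. The exact hypergeometric calculation (222 split 111:111) gives 7.9% with 67 men, 10.6% with 66, 10.7% with 111 and 14.0% with 110, hence about 8 to 14%.

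**5. What such a gap does to the unadjusted contrast in strength level.** Shift = gap × D.
- Gap of 10 points: 0.10 × 80 = 8 N to 0.10 × 150 = 15 N, i.e. 8 / 51.65 = 15% to 15 / 51.65 = 29% of the target.
- Gap at the 95% limits: 0.121 × 80 = 9.6 N to 0.132 × 150 = 19.7 N, i.e. 19 to 38% of the target. Gaps beyond these limits occur only about 5% of the time.

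**The case against.** The case for leaving the plan alone is substantial, and much of it stands.

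- **Validity.** A reader might infer that the trial is biased or that its false-positive rate is too high. Neither follows. Randomised 1:1 allocation with an unadjusted test is unbiased on average and keeps its type I error, and a subgroup analysis does not require stratified allocation.
- **Planned power.** A reader might infer that power is overstated. If the 20 preliminary participants were of both sexes, the SD of 114.19 N already contains the sex variance. The standard error with 111 per arm, 114.19 × √(2 / 111) = 15.3 N (95% ±30 N), then already pays for chance imbalance. The shift in step 5 is part of that error, not an addition to it.
- **Silence.** Section 2.3 never says that the sequence is unstratified; it names no stratum. A statistical analysis plan that is not shown could add a covariate. Still, section 2.8 does not leave the test open: it states an unadjusted one.
- **The sex subgroup analysis.** Comparisons within one sex cannot be shifted by a between-arm imbalance in sex, so that part of the plan already deals with it. Unequal splits cost little. At 63:48 among 111 men the efficiency loss is 1 − 4 × 63 × 48 / 111² = 1.8%; at 40:27 among 67 it is 1 − 4 × 40 × 27 / 67² = 3.8%. The subgroup analysis also covers all primary outcomes, not strength alone.
- **Level or change.** Section 2.1 speaks of improvement in flexion strength, which may mean change from baseline. A stable sex difference would then largely cancel. But the mean of 258.25 N reads as a level, and section 2.8 mentions neither change nor baseline, so the protocol does not settle this.

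What survives is narrower: a more precise analysis is available from data that the trial already collects, and the stated analysis does not use it.

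**Conclusion.** The point holds as a cheap improvement in precision and chance balance. It does not show bias, an inflated type I error, a wrong sample size or a sequence known to be unstratified, and it should not be read that way.

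Its size depends on the assumed sex difference and sex mix. Over the ranges used, power rises by roughly 3 to 10 percentage points (from 88.9% to between 91.9% and 98.8%), and a 10-point imbalance moves the unadjusted contrast in strength level by 15 to 29% of the target. If sex explains little of the variance, or if change from baseline is analysed, both the gain and the shift are smaller. The illustration concerns flexion strength; the documents give no figures from which to size the gain for the other primary outcomes.

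**What to change.** **Section 2.8.** Replace the unadjusted comparison of continuous primary outcomes with a linear model (ANCOVA) of the week-13 value on group and sex, and preferably on the baseline value collected under section 2.6. The subgroup analysis already requires sex to be recorded, so this needs no new data.

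**Section 2.3.** State whether the sequence is stratified. If it has not yet been produced, have the independent statistician generate it in permuted blocks within two sex strata, and keep sex in the model so that the analysis follows the randomisation. An unadjusted t-test after stratified allocation would be conservative.

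**Cost.** Two strata in the sequence program and one or two model terms. Sex must be known when an allocation is released, and arm sizes may differ slightly from 111/111. If recruitment has begun, the change to the analysis alone still delivers most of the gain.

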2.4 Intervention

2.4.1 Baduanjin exercise group

A 12-week Baduanjin exercise training (1 h per day from 5 p.m. to 6 p.m., 5 days per week) will be applied to the participants in the Baduanjin exercise group. Two qualified coaches who have engaged in the physical education over 5 years will teach the participants the correct Baduanjin postures according to the *Health Qigong - Baduanjin*, published by the General Administration of Sport of China. The ten postures are *Preparation posture, Prop up the sky with hands to regulate the triple* *energizer, Draw a bow on both sides like shooting a vulture, Raise single arm to regulate the Spleen (Pi) and Stomach (Wei), Look back to treat five strains and seven impairments, Sway head and buttocks to expel Heart (Xin)-fire, Pull toes with both hands to reinforce the Kidney (Shen) and waist, Clench fists and look with eyes wide open to enhance strength and stamina, Rise and fall on tiptoes to dispel all diseases*, and *Ending posture*.

2.4.2 Control group

The participants in the control group will not receive any specific training. They will keep their original exercises.

All participants will be required to record their daily activity or sport information during the intervention period, which is classified into low, moderate, or high intensity grade.

2.5 Follow-up

All participants will keep their usual exercises and record their daily activity or exercise information.

2.6 Outcome assessment

All primary and secondary outcomes will be assessed at baseline, 13 weeks (end of intervention), and 25 weeks (after the 12-week follow-up period).

2.6.1 Primary outcomes

• Lumbar muscle strength consists of flexion, extension, lateroflexion, and rotation myodynamia. It will be assessed with the *Tergumed Work Station* (produced by Proxomed GmbH, Germany; product type: Flexion Work Station:Tergumed Flexion; Lateral Flexion Work Station: Tergumed lateral Flexion; Extension Work Station: Tergumed Extension; Rotation Work Station: Tergumed Rotation) by experienced operators at the Evaluation Department of Rehabilitation Hospital Affiliated to FJTCM.

• Lumbar proprioception function will be measured by the *Prokin* proprioception evaluation and training system (produced by Tecnobody .S.r.l, Italy; product type: PK254P) by the Evaluation Department of Rehabilitation Hospital Affiliated to FJTCM.

• The Symptom Checklist-90 (SCL-90) will be used to measure self-reported symptom intensity.

• Stress will be measured with the Chinese Perceived Stress Scale (CPSS).

• Self-efficacy will be assessed with General Self-efficacy Scale (GSES).

• Attention will be assessed by Schulte Grid (8*8) test.

2.6.2 Secondary outcomes

• Physical fitness consists of cardiopulmonary function (including the step test, vital capacity, blood pressure, and heart rate), flexibility, and hand grip strength. It will be performed by the Department of Physical Education in FJTCM with physical fitness tester produced by Zhongtitongfang Co., Ltd., Beijing, according to the Chinese University Students’ Physical Health Standard.

• Mood and mindfulness will be measured by Profile of Mood States (POMS).

• The Self-Esteem Scale (SES) will be administered to measure self-esteem.

• Quality of life will be measured by the World Health Organization Quality of Life - BREF (WHOQOL-BREF).

• Quality of sleep will be measured by the Pittsburgh Sleep Quality Index (PSQI).

2.6.3 Safety measurements

Any adverse events related to Baduanjin, and how they are addressed, will be recorded during the intervention period.

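### Section 2.6.3 records only Baduanjin-related adverse events during the intervention, so the randomised comparison cannot answer the safety aim; the flow diagram conflicts with it on scope and period

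*Protocol*

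**What the plan says.** Section 1 (Study object) sets the primary aim: to "evaluate the effectiveness and safety of Baduanjin exercise on physical and mental health of college students through a rigorous randomization, parallel-controlled design". Safety is therefore tied to the comparison between arms.

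Section 2.6.3 holds the only rule for collecting harms: "Any adverse events related to Baduanjin, and how they are addressed, will be recorded during the intervention period". It does not say who judges relatedness, and it does not mention the control group.

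Section 2.4.2 describes the comparator: "The participants in the control group will not receive any specific training". Section 2.2.2 also excludes people for "being or having been engaged in a long-term regular practice of Baduanjin".

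The flow diagram (Figure 1, printed after Section 2.8) ends its list of post-intervention outcomes with "self-esteem, mood and mindfulness, quality of life, quality of sleep and adverse events", with no limit to related events or to one arm. After the 12-week follow-up it adds "Above outcomes assessment after follow-up period". Section 2.6 fixes baseline, week 13 and week 25 for primary and secondary outcomes only. Adverse events are in neither list, so Section 2.6 does not settle their timing.

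**The concern.** A parallel control arm serves a safety question by supplying the rate of sprains, back complaints and similar events that students would have had anyway. Here an event is recorded only if it is related to an exposure that one arm alone is assigned. The control arm then contributes almost nothing, and randomisation does no work for this part of the aim.

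What is left depends on attribution. Relatedness can hardly be judged without knowing whether the student practised Baduanjin. A background complaint in the exercise arm either counts against Baduanjin, with nothing to set it against, or is judged unrelated and never enters the record. The error can run either way.

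The flow diagram adds a practical problem: staff who follow it and staff who follow Section 2.6.3 would collect different events over different periods.

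**Working it through.** **The passages side by side**

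| Point | Section 2.6.3 | Flow diagram |
|---|---|---|
| Which events | related to Baduanjin | adverse events, no limit stated |
| Which arm | in effect the exercise arm | no limit stated |
| Period | intervention only | after intervention, and again after follow-up |

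Nothing in the protocol reconciles the two columns.

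**The denominator.** The protocol gives no figure for safety, only 111 per arm from the strength calculation in Section 2.1. With a difference of 0.20 × 258.25 = 51.65 N, SD 114.19 N, two-sided 5% and 90% power, n = 2 × [114.19 × (1.960 + 1.282) / 51.65]² ≈ 102.7, that is 103 against the 101 stated. This is close enough. Then 101 × 1.1 = 111.1, the stated 111. The point on adverse events does not depend on this calculation; 111 is used only as the arm size.

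**What the recorded difference estimates.** Let p1 and p0 be the true event risks with Baduanjin and control, and f the fraction of the Baduanjin arm's events that are attributed. The true difference is p1 − p0. The recorded difference is about f × p1 − 0, whatever p0 is. The two agree only if f = 1 − p0/p1, that is, if attribution happens to equal the unknown being sought.

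**False harm signal when p1 = p0 = p.** Section 2.8 compares outcomes between groups by chi-squared or Fisher's exact test at two-sided 0.05. For k/111 against 0/111, Fisher's P = 2 × C(111,k)/C(222,k):

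- k = 5: P = 0.060
- k = 6: P = 0.029

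Six attributed events are therefore enough. The count of attributed events is Binomial(111, f × p), and the chance of a false signal is P(X ≥ 6). Both p and f are assumptions:

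| True risk, both arms | f = 25% | f = 50% | f = 100% |
|---|---|---|---|
| 2% | <0.1% | 0.1% | 2.5% |
| 5% | 0.3% | 6% | 48% |
| 10% | 6% | 48% | 97% |
| 20% | 48% | 97% | >99.9% |

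With all events recorded alike in both arms, Fisher's false-positive rate at the same four risks is 0.6%, 2.3%, 3.0% and 3.4%.

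**Hidden harm.** Suppose p1 = 20%, p0 = 10% and f = 25%. The true difference is 10 percentage points. The recorded one is 0.25 × 20% − 0 = 5 points, half of it.

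**The case against.** Several points on the other side have force.

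- **A reader might infer that the control count is zero by definition.** The text does not go so far. Nothing forbids a control student from taking up Baduanjin, and the flow diagram places no arm limit on adverse events. What stands is that Section 2.6.3, followed as written, yields essentially no control events by design.
- **A reader might infer that attribution is made with the arm known.** The protocol does not say who judges relatedness. That whoever assesses relatedness would need to know the exposure is a strong inference, not a stated fact.
- **A reader might infer that a significance test on adverse events is planned.** Section 2.8 speaks of outcomes in general and does not name them. Safety has its own section outside the primary and secondary lists, and Section 2.6.3 could be read as descriptive reporting for the exercise arm. The false-signal figures are therefore conditional. Descriptive reporting would still supply no concurrent background rate, while Section 1 promises a controlled evaluation.
- **A single scenario would mislead.** At 10% risk with half attributed, the expected count is 111 × 0.10 × 0.5 = 5.55, which lies between a non-significant 5 and a significant 6. One P value from it would be too firm; the range is what can be shown. Participants are aged 18 to 25 and those with sports contraindications are excluded, so a low rate is plausible. At 2% with half attributed the false signal nearly disappears.
- **Loss of delayed events is not certain.** It follows from Section 2.6.3 but not from the flow diagram.

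None of this supplies a control-arm collection rule. The flow diagram is a label without a method, and an analysis plan cannot recover events that were never recorded.

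**Conclusion.** The point holds. The one operative rule for harms depends on an exposure assigned to a single arm and stops at the end of the intervention. The safety part of the primary aim therefore cannot be answered by the randomised comparison that Section 1 promises. Separately, Section 2.6.3 and the flow diagram conflict on scope and period and must be reconciled.

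The size cannot be fixed from the protocol, which gives neither an event rate nor an attribution fraction. With equal true risks of 2% to 20%, half of events attributed, 0/111 in controls and Fisher's test applied, the false-signal chance runs from 0.1% to 97%. At very low rates this consequence is small, but the missing background rate remains. The listed primary and secondary outcomes are unaffected. The matter should be settled before data collection, because the loss cannot be repaired afterwards.

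**What to change.** Amend Section 2.6.3 as follows:

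1. Record all adverse events in both arms, whatever their judged cause, from randomisation to week 25.
2. Use the same prompt for everyone in the activity record that Sections 2.4.2 and 2.5 already require through intervention and follow-up.
3. Enter the causality judgement as a separate field, so that it describes an event and does not decide whether it is recorded.
4. Report the proportion with at least one event by arm, with the risk difference and 95% CI.
5. Make Section 2.6.3 and the flow diagram agree on scope and period.

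The cost is one diary item, a short amendment, and more minor, unrelated events to enter.

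The change removes the dependence on attribution but does not make the answer precise. At an assumed 10% rate in both arms the half-width is 1.96 × √(2 × 0.1 × 0.9 / 111) = 0.079, about 8 percentage points. Power at 111 per arm would be about 29% for 5% against 10%, and 55% for 10% against 20%. The report should therefore present the interval and not read a non-significant result as proof of safety.
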